## 20.8 Vulnerable Populations

Prisoners, pregnant women and mentally impaired persons or any other individuals considered a Vulnerable Population will not be enrolled in this study.

## 20.9 Cost to Participants

Aside from travel to and from the study site, there will be no costs to research participants for participating in this research study. As part of their study participation, study participants will receive study visits with labs/assessments, including medical and

psychiatric screening, preparatory sessions prior to dosing, dosing with psilocybin or active placebo, and integration sessions following dosing at no cost.

## 20.10 Participant Compensation

Table 6 provides an itemized list of payment for study participation. Compensation will be prorated based on the extent of participation completed.

**Table 6:** Participant Compensation

Compensation is to be given within two months from end of trial for the particular subject.

| Activity                                                                                               | Compensation    |
|--------------------------------------------------------------------------------------------------------|-----------------|
| Screening: Informed Consent; remaining Screening activities; Baseline assessment; preparation sessions | SEK 500         |
| MRI1, PET1, Dosing session, MRI2, PET2, follow up assessments to day 42                                | SEK 2000        |
| LP1 and 2                                                                                              | SEK 1000        |
| Assesments day 43-365                                                                                  | SEK 1500        |
| TOTAL COMPENSATION                                                                              | SEK 5000 |

## 20.11 Treatment/ Compensation for Study Related Injury

The study participants are covered by Patientförsäkringen.

## 20.12 Protocol Deviations and Violations

All protocol violations and deviations must be addressed in study source and electronic documents, reported to the Sponsor, and must be sent to the site IRB per their guidelines. The site PI/study staff is responsible for knowing and adhering to their IRB requirements.

## 20.13 Record Retention

The PI must retain all study records required by the Sponsor and applicable ICH-GCP and MPA regulations in a secure and safe facility. The PI must consult a representative of the Sponsor before disposal of any study records. Essential documents are defined as documents that individually and collectively permit evaluation of the conduct of a trial and the quality of the data produced. These documents will be filed according to ICH-GCP regulations in the Investigator Site File (ISF).

## 20.14 Publication Policy

The Sponsor recognizes the importance of communicating medical study data and therefore encourages publications in reputable scientific journals and presentations at seminars or conferences.

- The results of this study may be published or presented at scientific meetings
- The Sponsor will comply with the requirements for publication of study results. In accordance with standard editorial and ethical practice, the Sponsor will generally

support publication of multicenter studies only in their entirety and not as individual site data. In this case, a coordinating PI will be designated by mutual agreement.

- Authorship will be determined by mutual agreement and in line with ICMJE authorship requirements.

## **21. CONFIDENTIALITY AND DATA SECURITY**

### **21.1 Confidentiality and Data Security at Research Site**

All participants will be seen in private rooms within a clinical or professional setting. Only the research coordinator, the Facilitators, and the participant will be present during the dosing session, with the exception of site PI and/or physician, as required.

Hard copies of study data will be kept securely, in a locked cabinet with limited and authorized access only.. Documents with identifiable information (including the informed consent) and blinding key will be filed separately from coded study data.

### **21.2 eCRF**

The electronic Case Report File (eCRF) platform used for this study will be Microsoft Access using a two-factor authentication Office 365 cloud solution. Part of the data will be directly entered into the eCRF whereas other data will be initially captured on paper. The source data table will define what data are initially collected on a paper/eCRF.

### **21.3 Take Care and 1177**

All information needed to comply with patientdatalagen will be documented in the Region Stockholm patient file system, Take Care (TC). Patient self-ratings will be performed via TC/1177.se and an *ansökan för uthämtning av personuppgifter* for extraction of study related data from TC will be performed before study start.

## **22. PREGNANCY**

### **22.1 Definitions: Women of Childbearing Potential (WOCBP)**

All individuals who were assigned biological sex of female at birth, and who have had no change in biological sex regardless of gender identification, will be considered Women of Childbearing Potential and will be required to have documented method of birth control and undergo urine pregnancy testing. For the purposes of this protocol, they will herein be referred to as “women”.

A woman is considered fertile following menarche and until becoming post-menopausal unless permanently sterile (see below).

Women in the following categories are not considered WOCBP:

1. Premenarchal

## 2. Premenopausal female with 1 of the following:

- Documented hysterectomy
- Documented bilateral salpingectomy
- Documented bilateral oophorectomy

Note: Documentation will be via self-report

## 3. Postmenopausal female

- A postmenopausal state is defined as no menses for 12 months without an alternative medical cause. A high follicle stimulating hormone (FSH) level in the postmenopausal range may be used to confirm a postmenopausal state in women not using hormonal contraception or hormonal replacement therapy (HRT). However, in the absence of 12 months of amenorrhea, a single FSH measurement is insufficient.
- Females on HRT and whose menopausal status is in doubt will be required to use one of the non-estrogen hormonal highly effective contraception methods if they wish to continue their HRT during the study. Otherwise, they must discontinue HRT to allow confirmation of postmenopausal status before study enrollment.

## 22.2 Contraception Guidance

### 22.2.1 Male participants

There are no restrictions on birth control choices/methods for male study participants.

### 22.2.2 Female participants

Women of childbearing potential are eligible to participate if they agree to use a highly effective method of contraception consistently and correctly as described in Table 7.

Documentation of birth control method will be obtained at Screening and confirmed at all follow up visits. Changes in birth control method will be documented. If there was a lapse in birth control coverage, additional pregnancy testing may be warranted.

**Table 7:** Highly Effective Contraceptive Methods

|                                                                                                                                                                                                                                                                       |
|-----------------------------------------------------------------------------------------------------------------------------------------------------------------------------------------------------------------------------------------------------------------------|
| Highly Effective Contraceptive Methods That Are User Dependent
Failure rate of <1% per year when used consistently and correctly.                                                                                                                 |
| Combined (estrogen and progestogen containing) hormonal contraception associated with inhibition of ovulation 
 
• Oral
 
• Intravaginal
 
• Transdermal
 
                                                 |
| Progestogen only hormonal contraception associated with inhibition of ovulation 
 
• Oral
 
• Injectable
 
                                                                                                        |
| Highly Effective Methods That Are User Independenta                                                                                                                                                                                                 |
| Implantable progestogen only hormonal contraception associated with inhibition of ovulation 
 
• Intrauterine device (IUD)
 
• Intrauterine hormone-releasing system (IUS)
 
• Bilateral tubal occlusion
 
 |

**Vasectomized partner**

*A vasectomized partner is a highly effective contraception method provided that the partner is the sole male sexual partner of the WOCBP and the absence of sperm has been confirmed. If not, an additional highly effective method of contraception should be used.*

**Sexual abstinence**

*Sexual abstinence is considered a highly effective method only if defined as refraining from heterosexual intercourse during the entire period of risk associated with the study intervention. The reliability of sexual abstinence needs to be evaluated in relation to the duration of the study and the preferred and usual lifestyle of the participant.*

## 22.3 Pregnancy Testing

- All WOCBP who were assigned biological sex of female at birth and have had no change in biological sex regardless of gender identification, will be required to undergo urine pregnancy testing.
- WOCBP should only be included after a negative highly sensitive urine pregnancy test.
- Pregnancy testing will be performed at Screening, Baseline, morning of dosing, Day 8, Day 42 and at any other time if it is suspected the participant may be pregnant.
- Pregnancy testing will be conducted using a commercial urine dipstick.

## 24. SUBSTANTIAL AMENDMENTS

Any substantial amendments in the protocol must be approved by the regional ethics committee and the regulatory authority (Läkemedelsverket) before implementation.

## 1. Introduction

The overarching purpose of this study is to conduct an initial examination of the safety, efficacy, tolerability and MDD relevant biological effects of single-dose psilocybin (3-[2- (dimethylamino)ethyl]-1H-indol-4-yl] dihydrogen phosphate) in otherwise medically healthy patients with recurrent MDD. The overall objectives of this study are to examine the efficacy of a single, fixed, 25 mg oral dose of psilocybin in reducing depressive symptoms and improving functional disability and quality of life in medically healthy patients with recurrent MDD when compared to active placebo; to compare the effect of biological markers of MDD in blood, CSF and using PET and MRI; to collect safety and tolerability data on single-dose psilocybin intervention in medically healthy patients with MDD, and to evaluate Facilitators' and participants' in-session behaviors on treatment outcome.

MDD is currently the leading cause of disability in the world. This highlights the urgent need to identify and test novel pharmacological agents that might benefit depressed patients who have not achieved symptom remission with currently approved antidepressant modalities. Recent studies suggest that psilocybin produces a substantial and sustained improvement in depressive symptoms following a single administration. It also highlights the need to identify the biological underpinning related to response to these novel treatments, in order to identify response markers and pave the way for rational drug development of novel antidepressant drugs.

## 2. Study objectives

The primary objective of this study is to evaluate the efficacy of a single 25 mg oral dose of psilocybin for recurrent major depressive disorder (MDD) compared to an active placebo (niacin) in otherwise medically-healthy participants ages 20 to 65, assessed as the difference between groups in changes in depressive symptoms.

### 2.1. Primary Objectives

The change in blinded rater Montgomery-Asberg Depression Rating Scale (MADRS) total score from Baseline to Day 8.

### 2.2. Secondary Objectives

The secondary objective is to evaluate the effect of psilocybin on synaptic density in prefrontal cortex and hippocampus, by comparing the change in [11C]UCB-J binding after psilocybin and placebo dosing.

### 2.3. Exploratory Objectives

The exploratory objectives of this study are to evaluate the efficacy of a single 25 mg dose of psilocybin for MDD compared to an active placebo in medically-healthy participants ages 20 to 65.

### 2.4. Safety Objectives

The overall safety objective of this study is to evaluate a single 25 mg oral dose of psilocybin compared to an active placebo in incidence, severity and frequency of Adverse Events (AEs), Treatment Emergent AEs (TEAEs), Solicited AEs, and Serious Adverse Events (SAEs) before, during and after the dosing session and at all follow-up visits.

## 3. Study Endpoints

### 3.1. Primary Endpoint

Between-group difference in change of blinded rater Montgomery-Asberg Depression Rating Scale (MADRS) total score from Baseline to post-dose Day 8.

### 3.2. Secondary Endpoints

The following secondary endpoints will be evaluated:

- Change in MADRS total score from Baseline to post-dose Day 15, 42, 180 and 365 (end of study) respectively
- Change in MADRS total score from Baseline to the treatment period (mean of Day 8-365)
- Change in MADRS-S score from Baseline to Day 365 (end of study)
- Change in MADRS-S score from Baseline to the treatment period (mean of Day 8-365)
- Response rate at all time points post dose (MADRS and MADRS-S)
- Remission rate at all time points post dose (MADRS and MADRS-S)
- Change in Sheehan Disability Scale (SDS) score from Baseline to Day 365 (end of study)
- Change in SDS score from Baseline to the treatment period (mean of Day 8-365)
- Change in Clinical Global Impression (CGI) score from Baseline to Day 8, 42, 180 and 365 (end of study) respectively
- Change in CGI score from Baseline to the treatment period (mean of Day 8-365)
- Time to initiation of antidepressant treatment

### 3.3. Exploratory Endpoints

Exploratory analysis will be between-group differences in:

- Change in p11 concentration in PBMC subsets from Baseline to day 15 Post dose
- Change in BDNF and VEGF concentration in plasma from Baseline to day 15 Post Dose
- Change in kynurenic acid in CSF from Baseline to day 15 Post dose
- Change in monoamine and monoamine metabolites in CSF from Baseline to day 15 Post dose
- Change in cytokine concentration (exact markers to be determined based on current literature at time of analysis) in CSF from Baseline to day 15 Post dose

- Change in metrics of whole-brain connectomics and hub characteristics of medial and ventrolateral prefrontal cortex as well as orbitofrontal cortex in the psilocybin treated group as compared to the placebo group, and in relation to clinical outcome (MADRS) as well as PET-outcome (resting state fMRI).
- Change in influence of top-down priors in an instructed fear learning paradigm and its relation to a change in activity of the ventromedial prefrontal cortex and lateral orbitofrontal cortex in the psilocybin treated group as compared to the placebo group, and in relation to clinical outcome (MADRS) as well as PET-outcome (tasked based fMRI).
- Change in Emotion detection under perceptual uncertainty and perspective-shifting ability in relation to large-scale network activity patterns in the psilocybin treated group as compared to the placebo group, and in relation to clinical outcome (MADRS) as well as PET-outcome.
- Change in anxiety symptoms from Baseline to post-dose Day 8, 15, 42 and 365
- Change in functional disability to post-dose Day 8, 15, 42 and 365
- Change in health-related meaning of life and satisfaction with life from Baseline to post-dose Day 8, 15, 42 and 365.
- Change in psychological flexibility from Baseline to post-dose Day 8, 15, 42 and 365
- Correlations between biomarkers and scales

### 3.4. Safety Endpoints

Differences between the psilocybin and active placebo groups in:

- Incidence of AEs by severity
- Incidence of AEs leading to termination from the study
- Incidence of TEAEs
- Incidence of TEAEs by severity
- Incidence of SAEs

## 4. Study Design

Thirty patients (males and females) ages 20 to 65 who, at Screening, meet ICD-10 criteria for recurrent MDD with a current depressive episode of at least a 30-day duration, an on-site Screening MADRS score 22 (consistent with moderate or greater depressive symptom severity), 30% symptom decrease from web-screen, and who meet all other inclusion/exclusion criteria at Baseline will be enrolled into the study and randomized with a 1-to-1 allocation under double-blind conditions to receive a single 25 mg oral dose of psilocybin or a single 100 mg oral dose of niacin. Expecting a maximum of 20% drop out rate a maximum of 6 more subjects may be randomized, in order to reach 30 patients completed (performed all study related activities up until and including PET#2 day 15). Niacin will serve as an active placebo that provides an acute physiological response (flushing) that may aid in blinding of intervention allocation. All randomized participants will be included in the Full Analysis Set (FAS) that will be used for analyzing primary and secondary study endpoints.

Randomization will occur for participants who have been determined to be eligible for the study and will occur the morning prior to dosing. Following this, participants will be randomized to one of two intervention groups. Participants are randomized in blocks in a 1:1 ratio in a blinded fashion to the psilocybin group or the active control group. The block size will not be shared. Randomization will be done at the site by strictly following a randomization list in sequential order. If a patient is replaced the new patient will be allocated a randomization number with the same treatment while keeping the double blinded allocation. This will be performed by having back-up blinded treatment allocations for each subject in sealed envelopes. These will only be used and opened following withdrawal. Importantly, the allocated treatment will remain blinded for both the withdrawn and replacement subject as well as for the study team.

## 5. Statistical analysis

### 5.1. Power analysis and Sample Size Determination

The difference between psilocybin and placebo in change from baseline to Day 8 in MADRS total score (primary endpoint) will be analyzed for the Full Analysis Set using Analysis of Covariance including treatment as main effect and baseline as covariate.

Based on prior controlled studies of psilocybin in cancer- related depression and anxiety, a decrease in depression symptoms from baseline to one-week post-dose of at least 30% is expected in the placebo

arm. In an open-label study of psilocybin the change in MADRS total score from baseline to 1 week was -23.3. Several clinical studies in the literature report a standard deviation in change in MADRS total score around 10.

A sample size of 15 in each group will have 80% power to detect a difference in means of 11 (the difference between a psilocybin mean, of -23 and a placebo mean, of -12) assuming that the common standard deviation is 10 using a two group t-test with a 5% two sided significance level.

Considering the short duration between treatment and primary endpoint measurement day 8 the risk of withdrawal is considered low. The total sample size is set to 30 patients completing day 15. In case of withdrawals before day 15 additional patients may be randomized to ensure 30 patients included in the primary and secondary analyses. Estimating a maximum of 20% withdrawals, a maximum of 6 additional subjects can be included.

## 5.2. General statistical considerations

Efficacy analyses of primary, secondary, and exploratory outcomes will be conducted using the Full Analysis Set (FAS) population and the Safety set will be used in all safety analyses. All participants randomized to receive a study intervention (psilocybin vs. active placebo) will be included in FAS. All participants randomized to receive a study intervention (psilocybin vs. active placebo) with no relevant protocol deviations will be included in per protocol (PP). The Per Protocol set will be used in sensitivity analyses for the primary and secondary objectives. All participants who have received study treatment will comprise the overall safety set.

All reported p values will be two-sided, and  $p < 0.05$  will be considered statistically significant. However, any hypothesis that includes a direction of change will be tested using one-sided test using a significance level of 0.025. The analysis will not be adjusted for multiple comparisons and the analysis should be described and interpreted as exploratory analysis. All data management and analyses will be performed using SAS 9.4 and R version 3.6.1.

### 5.3. Descriptive statistics

Demographic, diagnostic, baseline, line of therapy and safety data will be presented using descriptive statistics. Continuous variables will be described by the number of patients with a recorded value, mean with standard deviation and when appropriate also 95% confidence interval (CI), median, upper and lower quartiles and maximum and minimum values. Categorical variables will be reported as number and percentages with 95% CIs. Differences between subgroups will be compared using chi-square tests, and fisher's test if few cases, for categorical variables and using t-test, and non-parametric statistics, for continuous variables. Distributional features of all measurements will be evaluated, and data transformation (e.g., logarithm, rank transform) will be performed when applicable. Missing data will be described in all summaries.

### 5.4. Primary analysis

The primary endpoint is change from baseline to Day 8 in MADRS total score. The primary analysis will be a mixed-model repeated measures (MMRM) model, fitting treatment, timepoint, and a treatment\*timepoint interaction. An unstructured covariance matrix will be used to estimate the within subject variation and the Kenward-Roger approximation will be used to estimate denominator degrees of freedom. If this analysis fails to converge, the following structures will be used in order: heterogeneous Toeplitz (TOEPH), Antependence (ANTE1), heterogeneous autoregressive (ARH1), Autoregressive (AR1) and Compound symmetry (CS). The first covariance structure yielding convergence will be used. If a structured covariance is used, the empirical "sandwich" estimator of the standard error (SE) of the fixed effects parameters will be used to deal with possible model misspecification of the covariance matrix. The "least squares" mean (LS mean) estimates of treatment differences and their 95% CIs will be presented for each time point. In addition, a p-value will be presented for the primary comparisons. The LS mean change from baseline to each post-baseline will be plotted by treatment group. To examine the pattern of missing data, the number and percentage of subjects with a mean MADRS score will be presented by treatment group. Summary statistics for MADRS score and change from baseline will also be presented, based on observed scores (no imputation of missing data) calculated from all available data. These summaries will also be produced for the subset of subjects who have a non-missing MADRS score.

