#### 16.4.1 Efficacy Analyses

The difference between psilocybin and placebo in change from baseline to Day 8 in MADRS total score (primary endpoint) will be analyzed for the Full Analysis Set using Analysis of Covariance including treatment as main effect and baseline as covariate. The same method will be applied for all other single measure endpoints. Treatment differences of multiple measurement endpoints will be analyzed by the mixed model repeated measurements analysis (MMRM) method.

Response and remission rate will be analyzed using logistic regression with the baseline measure as a covariate. The adjusted percentage with 95% CI, Odds Ratio with 95% CI and nominal p-values for the treatment comparison will be presented.

Time to initiation of antidepressant will be defined as the time (in days) from day 43 to the date when any antidepressant has been prescribed. Kaplan-Meier plots of time to initiation of antidepressant will be displayed by treatment groups. Time to initiation of antidepressant will be censored at study discontinuation or completion.

If the assumption of normality does not hold for a particular endpoint on the original scale of measurement, nonparametric methods (e.g. Mann Whitney U test, Fisher's exact) or common transformations (e.g., ln, sqrt) of the original data may be used.

P-values less than 0.05 will be considered statistically significant. As default all tests will be two-sided and two-sided 95% confidence intervals will be computed for the treatment difference. However, any hypothesis that includes a direction of change, eg *increased* [11C]UCB-J binding after dosing, will be tested using one-sided test using a significance level of 0.025.

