## 5.5. Sensitivity analysis

The secondary endpoints evaluating changes in (MADRS, MADR-S, SDS, and CGI) score during different/several time points will be conducted by using MMRM models, fitting treatment, timepoint, and a treatment\*timepoint interaction. The models will be built as of the primary endpoint (see 5.4 Primary analysis). Paired t-test will be performed for between-groups comparisons at all time points, and between all time points over time against baseline. Response will be defined as  $\geq 50\%$  decrease (MADRS and MADR-S) compared to the last measurement before dosing, and remission will be defined as a (MADRS and MADR-S) score  $\leq 10$ . In addition, response will also be defined as  $> 10$  points decrease (MADRS and MADR-S) compared to the last measurement before dosing. Response and remission rate at all time points post dose will be analyzed by using Fisher's exact test and univariable logistic regression with odds ratios (OR) and their 95% confidence intervals (CI) and nominal p-values. An additional secondary endpoint will be time to initiation of antidepressant treatment. Time to initiation of antidepressant will be defined as the time (in days) from day 43 to the date when any antidepressant has been prescribed. Subjects will be censored at study discontinuation or completion. The Kaplan-Meier approach will be assessed with the log-rank test.

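### The Day 8 MADRS primary analysis is defined both as a baseline-adjusted ANCOVA and as an MMRM without a baseline covariate, and nothing says which governs

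*Protocol*

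**What the plan says.** **ANCOVA.** Protocol 16.4.1 analyses the change from baseline to Day 8 in MADRS total score "using Analysis of Covariance including treatment as main effect and baseline as covariate". The synopsis (Statistical Analysis) and protocol 16.1 say the same. SAP 5.1 repeats it: the difference "will be analyzed for the Full Analysis Set using Analysis of Covariance including treatment as main effect and baseline as covariate". Protocol 16.4.1 extends ANCOVA to the other single-measure endpoints and gives MMRM a separate role: "Treatment differences of multiple measurement endpoints will be analyzed by the mixed model repeated measurements analysis (MMRM) method".

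**MMRM.** SAP 5.4 opens with the same endpoint ("The primary endpoint is change from baseline to Day 8 in MADRS total score") and continues: "The primary analysis will be a mixed-model repeated measures (MMRM) model, fitting treatment, timepoint, and a" treatment-by-timepoint interaction. It specifies the covariance structure, its fallbacks and Kenward-Roger degrees of freedom. It lists no baseline covariate and no set of visits.

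**Related open choices.** If normality does not hold for an endpoint, protocol 16.4.1 says that "nonparametric methods (e.g. Mann Whitney U test, Fisher's exact) or common transformations (e.g., ln, sqrt) of the original data may be used". It gives no criterion and does not exempt the primary endpoint. For the binary endpoints the protocol says: "Response and remission rate will be analyzed using logistic regression with the baseline measure as a covariate". In SAP 5.5 the same rates are "analyzed by using Fisher's exact test and univariable logistic regression".

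**The concern.** The trial has one primary endpoint, a stated null hypothesis (protocol 16.3) and a sample size built on a single two-sided 5% test. Two different models are each named for that test. They can give different estimates, intervals and verdicts from the same 30 patients. They also treat a missing Day 8 score differently: ANCOVA drops the participant, whereas the MMRM keeps anyone with another post-dose MADRS score. If the choice is still open when the data are unblinded, a reader cannot tell which p-value was planned. If SAP 5.4 is followed as written, the trial also loses the precision gain of the baseline covariate that the protocol promised.

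**Working it through.** **Inputs from the documents** (protocol 16.1, SAP 5.1): 15 per arm, difference 11, SD of change 10, two-sided 5%, two-group t-test. **Assumed:** absolute correlation r between baseline MADRS and change. The documents do not give it, so it is taken from 0 to 0.7 with the SD of change held at 10.

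**1. The plan's own figure.** SE = 10 × √(2/15) = 3.65, and the noncentrality is 11/3.65 = 3.01 on 28 df. Power is 82.8%. With 14 per arm it is 79.99%, so 15 is the smallest number that reaches 80%. The sample size is reproduced.

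**2. MMRM as written in SAP 5.4.** With complete data, an unstructured covariance and only treatment, timepoint and their interaction, the Day 8 contrast is the difference in mean change with the pooled Day 8 variance. That is the two-group t-test. A numerical check of this form gave t = -2.593 both ways, on 28 df. Power is therefore 82.8% at every r, and the 95% CI half-width is 2.05 × 3.65 = 7.48 points.

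**3. ANCOVA with baseline.** Residual SD = 10 × √(1 − r²), on 27 df. For r = 0.5: 10 × √0.75 = 8.66; noncentrality 11/(8.66 × 0.365) = 3.48; power 91.8%. The formula ignores the small cost of chance baseline imbalance. The simulated column includes it.

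**4. Disagreement and picking.** Simulated normal data, 15 per arm, 20,000 runs under the null and 8,000 under each alternative. The unadjusted test had simulated power of about 83% throughout at a difference of 11.

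| r | Residual SD | ANCOVA power, formula | ANCOVA power, simulated | CI half-width | Verdicts differ, true difference 11 | Verdicts differ, true difference 7 | Type I, better of two | Type I, best of three (with Mann-Whitney) |
|---|---|---|---|---|---|---|---|---|
| 0 | 10.00 | 82.7% | 81.3% | 7.49 | 3.7% | 5.3% | 5.8% | 6.5% |
| 0.3 | 9.54 | 86.1% | 85.1% | 7.15 | 6.4% | 10.1% | 6.0% | 6.5% |
| 0.5 | 8.66 | 91.8% | 91.4% | 6.49 | 11.7% | 18.6% | 7.0% | 7.6% |
| 0.7 | 7.14 | 98.2% | 97.8% | 5.35 | 16.1% | 32.8% | 8.3% | 9.0% |

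The last column lets Mann-Whitney be chosen freely. Protocol 16.4.1 makes it conditional on non-normality, so that column is an upper end for picking among these three tests.

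**The case against.** The best defence is that SAP 5.1 merely repeats the protocol's sample-size text, while SAP 5.4 carries the heading for the primary analysis and is the natural operative text. That would settle the conflict inside the SAP. It does not settle the conflict with protocol 16.4.1, which is itself an analysis section, names ANCOVA for this endpoint and keeps MMRM for repeated measurements. No precedence rule is stated. SAP 5.5, although titled as sensitivity analysis, deals with secondary endpoints. The only sensitivity analysis stated for the primary objective is the per-protocol set.

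Four stronger readings are tempting, and the documents do not support them.

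- A reader might infer that the MMRM throws baseline MADRS away and leaves chance imbalance uncorrected. Its outcome is change from baseline, so baseline is subtracted with a coefficient of one. What is missing is the adjustment by an estimated slope, and the planned power survives.
- A reader might call this the trial's single confirmatory test. Protocol 16.4.2 and SAP 5.2 describe the endpoints and analyses as exploratory. A primary endpoint still needs one model.
- A reader might fear two Day 8 results, one after Day 42 and one after Day 365. Protocol 16.4.4 fixes the primary analysis at Day 42 completion, and 9.10.1.1 limits that release to phase A data, which largely answers the point.
- A reader might take the normality clause as a plan to switch after seeing results. It is conditional and no timing is given. The fault is only that it has no criterion and does not exempt the primary endpoint.

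The response and remission models are secondary, with nominal p-values, and do not affect the Day 8 test.

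**Conclusion.** The contradiction is real and should be settled before unblinding. The sample size is not in error, and following SAP 5.4 would not take power below plan. The cost of omitting the covariate runs from nothing at r = 0, where adjustment is in fact very slightly worse, to about 15 percentage points of power at r = 0.7. The possible type I inflation is moderate: about 6% to 8% for the better of the two models, and up to about 9% with the rank test added. These sizes rest on the assumed r, normal data, complete follow-up and an SD of change of 10. The inflation figures describe what the wording permits, not something the documents show is intended. The open normality clause and the loss of baseline from the SAP's response and remission models are genuine but secondary.

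**What to change.** Name one baseline-adjusted primary model, in the same words, in the synopsis, protocol 16.1 and 16.4.1, and SAP 5.1 and 5.4. Either of these would do:

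- the Day 8 ANCOVA with treatment and baseline MADRS; or
- the Day 8 treatment contrast from an MMRM on change from baseline that adds baseline and baseline-by-timepoint and uses only the post-dose phase A visits (Days 8, 15 and 42).

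Label the other a sensitivity analysis. State that any rank-based or transformed analysis of the primary endpoint is supportive only. Restore the baseline covariate in the response and remission logistic models of SAP 5.5, as protocol 16.4.1 has it.

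The cost is an edit to protocol and SAP text. It needs no new data, visits or patients, but it is credible only if it is made and dated before the blind is broken.
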